### Visit 3: Second Initial Testing Visit – Emulator or Actual Feet (approximately 3 hours)

At this visit participants will be asked to repeat the study procedures described above in Visit 2; they will complete the procedures using the equipment (PFE or actual feet) that they did not use during Visit 2 (based on randomization as described above).

At the end of this visit, the prosthetist will fit participants with one of the three actual feet that they used earlier; foot order will be randomized again and participants will remain blinded to foot condition (lightweight fabric will be secured around any potentially identifying features of the prosthetic foot using zip ties). Participants will wear the assigned study prosthetic foot (connected to their prescribed socket) for the next one week at home and in the community. Participants will be scheduled to return for a follow-up visit after this one-week period. Designated study staff will store the participants' prescribed prosthetic foot in a designated, secured cabinet within a locked office until they have completed the study or choose to stop their participation. Participants will be instructed to contact us if they have any concerns or discomfort associated with their prosthetic limb. If needed, participants can come in for prosthetic alignment adjustments during the 1 week in home/community test window. Alternatively, participants may also see their own prosthetist for adjustments, if needed, during the test window. In this case, study staff will make note of the necessity for the change and the clinic that the participant visited.

Note that prosthetic alignment will be optimized under all foot conditions.

### Visits 4, 5 and 6: Follow-up Testing Visits (up to 4 hours each)

During each of these visits, participants will be asked to complete a survey that includes questions about their preference, stability, perceived foot stiffness, satisfaction, balance, activity restrictions, fear of falling, and mobility while using the study assigned prosthetic foot that they wore for the past week. During each of these visits, participants will be asked to repeat some of the performance-based balance-related outcome measures (i.e., FSST, 4SBT, NBWT, L test) (as described under Visit 1, with the only difference being that participants will be wearing the respective study prosthetic foot during visits 4, 5, and 6).

Furthermore, during these visits, a 16-camera motion capture system (Vicon Motion Systems Ltd., Oxford, UK) or an IMU system (XSens, Movella Inc., Henderson, NV, USA) may be used to collect positional data, using the same procedures described above in visits 2-3. Up to eighty reflective markers, or up to twenty-five IMUs, will be placed on anatomical locations (e.g., arms, legs, torso) and corresponding measurements will be taken (e.g., leg length, ankle width) according to the Vicon Full Body Plug-In Gait method. No data will be shared with Vicon Motion Systems Ltd. or Movella Inc. Participants may be asked to repeat some of the previous study procedures (i.e., walking conditions) while biomechanics data is being collected. Specifically, they may be asked to repeat

some of the previous study activities, including standing and walking trials overground and on the level, inclined, cross-slope, and uneven treadmill conditions (see details above, depending on their LM or HM group assignment) at their self-selected comfortable, slow, and fast walking speeds using the study foot that they have accommodated to following their one-week at home trial. As is standard for gait biomechanical data collection, the infrared motion capture cameras will collect marker coordinate data during walking if using the marker-based motion capture system. Embedded force platforms may also be used to collect synchronized ground reaction force data. The participants will be allowed to rest as much as needed between or during study activities.

At the end of Visits 4 and 5, the prosthetist will fit participants with one of the other remaining prosthetic feet (based on their randomized foot order and participants will remain blinded to foot condition). Participants will wear the assigned prosthetic foot (connected to their prescribed socket) for the next one week at home and in the community. Again, participants will be scheduled to return for a follow-up visit after one week. Participants will be reminded to contact us if they have any concerns or discomfort associated with their prosthetic limb. If needed, participants can come in for prosthetic alignment adjustments during the one-week in home/community test window. Should it not be feasible for the participant to come in to a study site (e.g., VAPSHCS) for alignment adjustments, study staff can recommend that the participant see their local prosthetist for any necessary changes. In this case, study staff will make note of the necessity for the change and the clinic that the participant visited.

Testing procedures will be repeated again at Visit 6. At the end of Visit 6, the prosthetist will re-fit the participants' prescribed prosthetic foot, which will conclude the testing sessions.

#### Visit reminders

Designated study staff may call and/or send a visit reminder email to participants prior to each study visit.

#### VA Puget Sound only: Repository (optional)

We may ask participants if they want to add their data (without identifiers) from this study to our data repository ([name], MIRB #00493). Interested participants will be asked to sign a separate Consent Form for the repository.

#### Photos and video recording

With the participant's explicit consent, we may take video and photos during portions of this study, for documentation and use in dissemination efforts or educational materials. All videos and photos will exclude the participant's face and any identifying marks will be covered. If any identifiable features or marks are mistakenly captured they will be anonymized during data processing; the participant's face or other unique marks would be blurred prior to any use outside of the research team that captured the images. Videos will be recorded without

sound so that we do not capture any voice prints. If a participant's voice is accidentally recorded that section of video would be altered prior to any use outside of the VA study team. Participants will be able to opt out of this activity and still participate in the study.

## **2.6 Data Analysis**

### Statistical Analysis

For both H1.1 and H1.2 (see Objectives section, 1.0 above for hypotheses details), linear mixed effects regression will be used to assess the association between Perceived Stability score, MOS, ABC, NBWT, or FSST (the dependent variables) and prosthetic foot (the independent fixed effect) with random effects for study participant. For H2.1 linear mixed effects regression will be used to test for correlation between Perceived Stability score for the emulated foot (the independent fixed effect) and follow-up Perceived Stability score for the corresponding actual foot (the dependent variable) with study participant as a random effect. For H2.2, similar models will be used to test for associations between the Perceived Stability score in the emulated foot (the independent fixed effect) and follow-up ABC, NBWT or FSST in the actual foot (the dependent variable). For H3.1 and H3.2, linear mixed effects regression will be carried out as above with initial Perceived Stability score as the independent fixed effect and Perceived Stability score, ABC, NBWT or FSST as the dependent variables with participant as the random effect. Linear mixed effects regression provides a more flexible approach to analyze repeated measures data compared to the traditional repeat measures models, with fewer model assumptions and the ability to incorporate data from participants who do not complete the study. These models account for non-independent data due to within-participant repeated measures by estimating separate between- and within-participant errors. For all models, mean and standard errors of the outcomes for each prosthetic foot and pair-wise mean differences and 95% confidence intervals (CI) across the three feet will be estimated and tested for significance.

Power Analysis: Sample size for this study was based on pilot data collected in support of Specific Aim 1. Power analysis was carried out for two of the primary study variables: NBWT and MOS (H1.1 and H1.2). For NBWT we obtained overall mean, between and within participant variances based on pilot data for 45 participants testing for differences in NBWT using a multi-axial/split-toe foot (n=34) vs. a solid keel foot (n=11). Participants using the former foot walked a mean 3.4 ft farther than participants using the solid keel foot, with between and within participant standard deviation (SD) 4.1 and 2.7, respectively. Using these estimates, we simulated 5000 datasets of NBWT with sample size equal to 40 and 50 participants, each wearing all 3 feet (within-participant design), and with 1 mean pair-wise difference in NBWT of 2 ft; smaller differences than found in the pilot data as that study estimated between-participant differences which tend to be larger. For each dataset, linear mixed effects regression was carried out as described in the methods section, and power was estimated based on a type 1

error of .01, as we have 5 outcomes of interest. We estimate 81% and 91% power to detect differences in NBWT of 2 ft. for sample sizes of 40 and 50 respectively. Using estimates obtained from Gates et al (2013), we simulated MOS in participants with TTA walking on uneven surfaces, using 8.3 cm, 1.9 cm and 1.0 cm as the mean, between-participant and within-participant SDs respectively using a similar procedure as above. We estimate 98% power to estimate a pair-wise difference between prosthetic feet of 1 cm for 40 participants, and 87% power to estimate a difference of 0.7 cm for 50 participants. Considering the potential for attrition, we will recruit 60 participants (30 at each site), so that even if 20% of the recruited participants drop out (a conservative estimate based on the <5% drop out rate in our current emulator study with the same number of study sessions), we will still have enough participants for adequate statistical power. This will also allow us to accommodate a higher drop-out rate and those who are deemed ineligible after signing consent during physical examination screening without a modification.

All statistical analysis will be performed by study staff with de-identified data. No PHI or VA sensitive data will be analyzed or shared across sites. De-identified data files will also be sent off-site to our biostatistician (VA research staff) and among staff and study collaborators across study sites. These will be sent via email and will only contain de-identified data. For example, de-identified data which has been exported from VA REDcap behind the VA firewall for data analysis. Only de-identified data will be disclosed outside of the VA. A copy of the de-identified data set will be sent off-site to our biostatistician, so that they may assist with data analyses. Our biostatistician will not have access to the key to the study codes/crosswalk or to any PHI. Our offsite collaborators (Drs. [name], [name], and [name]) may receive copies of data analyses summary reports (all de-identified) so that they may assist with data interpretation and manuscript preparation.

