### ***Specific Aim 2: Determine whether a multiaxial prosthetic foot emulator can be used to predict stability and balance-confidence outcomes with corresponding commercial prosthetic feet in Veterans with TTA.***

*H2.1:* Participants' initial perceived stability with each emulated foot will correlate with their perceived stability with the corresponding actual foot at follow-up.

*H2.2:* Participants' initial perceived stability with each emulated foot will correlate with their balance confidence (i.e., ABC) and stability (i.e., NBWT and FSST) in the corresponding actual foot at follow-up.

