### ***Specific Aim 3: Determine whether a brief trial of commercial prosthetic feet can predict longer-term stability and balance-confidence outcomes in Veterans with TTA.***

*H3.1:* Participants' initial perceived stability with each actual foot (relative to other feet) will correlate with their perceived stability with the corresponding foot at follow-up.

H3.2: Participants' initial perceived stability with each actual foot will correlate with their balance confidence (i.e., ABC) and stability (i.e., NBWT and FSST) in the corresponding foot at follow-up.

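### The Aim 2 and 3 models contain no foot term, so average foot differences load onto the slope and a significant slope cannot show that a participant's own test-drive rating predicts that participant's result

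*Protocol*

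**What the plan says.** Protocol 2.6, Statistical Analysis, specifies the models aim by aim.

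- **H1.1 and H1.2:** the outcome is related to foot, "and prosthetic foot (the independent fixed effect) with random effects for study participant".
- **H2.1:** the model relates "Perceived Stability score for the emulated foot (the independent fixed effect) and follow-up Perceived Stability score for the corresponding actual foot (the dependent variable"), with participant as a random effect. H2.2 uses similar models for ABC, NBWT and FSST.
- **H3.1 and H3.2:** the same approach, "with initial Perceived Stability score as the independent fixed effect and Perceived Stability score, ABC, NBWT or FSST as the dependent variables", again with participant as the random effect.
- **Closing sentence:** "For all models, mean and standard errors of the outcomes for each prosthetic foot" are to be estimated, together with tested pair-wise differences across the three feet.

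The hypotheses (1.0 Objectives) are worded as correlations. H2.1 reads "Participants' initial perceived stability with each emulated foot will correlate with their perceived stability with the corresponding actual foot at follow-up". H3.1 reads "Participants' initial perceived stability with each actual foot (relative to other feet) will correlate with their perceived stability with the corresponding foot at follow-up". Neither says whether the correlation must hold beyond average differences between feet.

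**The concern.** Specific Aim 1 expects foot stiffness to move Perceived Stability and also ABC, NBWT and FSST. Perceived Stability is the predictor in Aims 2 and 3, and these measures are the outcomes. If one foot is better for everybody, its initial ratings and its follow-up results are both high, and the slope is positive even when no participant's own rating carries information about that participant.

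The foot-average part of the slope rests on three foot means per mobility group. The model nevertheless treats it as supported by 48 × 3 = 144 rows that are independent given participant.

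What is at stake is the reading of the result. A test drive adds something for the individual only if it informs beyond knowing which foot does best on average. The listed slope cannot tell these apart. Separately, a model whose only fixed effect is the score has no foot parameter, so it cannot give the foot means and contrasts promised for all models.

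**Working it through.** **Inputs (Protocol 2.6, Power Analysis).** Three feet per participant; NBWT planning difference 2 ft; between- and within-participant SD 4.1 and 2.7 (ratio 1.52); MOS planning difference 1 cm with within-participant SD 1.0 cm; 60 recruited less 20% = 48 completers; type 1 error .01 in the power analysis, 95% intervals in the analysis text. In within-person SDs the planning differences are 2 / 2.7 = 0.74 (NBWT) and 1 / 1.0 = 1.0 (MOS). The Protocol gives no SD or foot difference for Perceived Stability, so the score is assumed to shift by the same number of within-person SDs as the outcome. That assumption is varied below.

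**Step 1: reproduce the plan's own power.** The Power Analysis simulates "with 1 mean pair-wise difference in NBWT of 2 ft". With one foot differing by d, the 2-df foot test has noncentrality N × (2/3) × (d / SD_within)². Power at .01 by noncentral F / chi-square:

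| Case | Noncentrality | Recomputed | Stated |
|---|---|---|---|
| NBWT 2 ft, N=40 | 40 × 0.667 × 0.549 = 14.6 | 79.6 / 82.6% | 81% |
| NBWT 2 ft, N=50 | 50 × 0.667 × 0.549 = 18.3 | 90.0 / 91.6% | 91% |
| MOS 1 cm, N=40 | 40 × 0.667 × 1 = 26.7 | 98.2 / 98.8% | 98% |
| MOS 0.7 cm, N=50 | 50 × 0.667 × 0.49 = 16.3 | 85.5 / 87.5% | 87% |

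The stated figures are reproduced to within 2 points, so one foot standing apart is the plan's own scenario. No power or error rate is stated for the Aim 2 and 3 slopes.

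**Step 2: the slope that foot averages alone create.** Let score and outcome share only the foot shift d (in within-person SDs). The foot deviations are −d/3, −d/3, 2d/3, with sum of squares 2d²/3. The within-person error contributes 2. The expected within-person slope is (2d²/3) / (2d²/3 + 2) = d² / (d² + 3), which is 0.5476 / 3.5476 = 0.154 at d = 0.74 and 1 / 4 = 0.25 at d = 1.0. None of it is participant-specific.

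At d = 0.74 and N = 48, Sxx = 48 × 2.365 = 113.5 and the residual variance is 1.1825 × (1 − 0.154²) = 1.154. The SE is √(1.154 / 113.5) = 0.101 and z = 0.154 / 0.101 = 1.53. Rejection at 5% is about Φ(1.53 − 1.96) = 33%. Simulation with a person-mean-centred score gives the same 33%. The model as listed also mixes in the between-person slope, here zero, so its slope is smaller (0.106 simulated) and it rejects somewhat less often.

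**Step 3: simulated size of the listed model.** Random-intercept REML, Wald test, 48 completers, no participant-level or between-person link, one foot differing equally in score and outcome:

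| Shift (within-person SD) | No foot term, nominal 5% | No foot term, nominal 1% | Foot in model, nominal 5% |
|---|---|---|---|
| 0 | 5–6% | 1% | 5% |
| 0.25 | 5% | 1% | 5% |
| 0.5 | 10–11% | 3% | 5% |
| 0.74 | 24–28% | 10–12% | 5–6% |
| 1.0 | 56–57% | 31–33% | 5–6% |

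Ranges are across independent runs.

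- N from 40 to 60: 21–29% at 0.74 SD and 47–65% at 1.0 SD.
- Equally spaced feet: 16% and 38% (0.74 and 1.0 SD).
- Outcome shift held at 0.74 SD, score shift varied: 11% at 0.4 SD and 40% at 1.0 SD.
- Foot shifts only the score or only the outcome: nominal (4.8–5.3%).

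**Step 4: which foot term works.** Protocol 2.5 (Visit 1) gives each mobility group three feet with one shared, so there are 3 + 3 − 1 = 5 feet but 2 × 3 = 6 group-by-foot cells. Groups are formed largely by walking distance and may differ in both score and outcome. A five-level foot factor without group rejects about 10% at a group gap of 1.5 within-person SD and about 52% at 3. The six cells hold about 5–6% throughout.

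**The case against.** **The hypotheses say only that scores correlate.** A foot rated better on the emulator and later better in use is then the predicted finding, and the rejections above are true positives. This stands for a total correlation. It does not stand for a claim about the individual, which the test-drive purpose and H3.1's comparison among feet point to without stating it.

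**The closing sentence may mean that foot is in every model.** That reading is possible, and a fuller model list may sit in a statistical analysis plan not shown here. But it conflicts with the fixed effects named for Aims 2 and 3, so the section needs reconciling either way.

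**The inflation is conditional.** This also stands. A reader might infer that the slope test always rejects far above its nominal level, or that success in Aim 1 makes Aims 2 and 3 succeed automatically. The documents do not support either. Sizeable shifts are needed in both score and outcome, and even at 0.74 SD most simulated trials do not reject. Using the pilot's 3.4 ft (1.26 SD) gives rates of 84 to 90%, but the Protocol itself discounts that figure as a between-participant difference and plans on 2 ft.

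**A foot term discards signal.** With a true within-person correlation of 0.2 and 0.74 SD foot shifts, rejection falls from about 83% to 42%. What is lost is the contribution of shared foot averages. When feet do not differ, the same correlation is detected about 40% of the time with or without the term.

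**Conclusion.** The point holds in conditional form. As listed, the H2.1 to H3.2 slopes mix shared foot differences with individual prediction, and a significant slope cannot establish the latter. At the plan's own NBWT difference the test rejects about 24–28% at nominal 5% with no participant-level link; at the MOS planning difference, about 57%; at 0.5 SD, 10–11%; and at the nominal rate if foot shifts neither variable or only one.

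These figures assume the same shift in Perceived Stability as in the outcome, one foot standing apart, and 48 completers. They are error rates only for individual prediction. The mismatch between these models and the promised per-foot estimates holds regardless of any assumption. The Aim 1 power figures are unaffected.

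One limit applies: a foot term removes foot averages only. A link between participants' overall levels is untouched (with a between-person correlation of 0.5 and no foot effect, rejection is about 46% with or without foot).

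**What to change.** In 2.6, Statistical Analysis:

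1. In the H2.1, H2.2, H3.1 and H3.2 models, add prosthetic foot as a categorical fixed effect within mobility group (six group-by-foot cells), beside the initial Perceived Stability score and the participant random effect.
2. State that any claim of individual prediction rests on the score coefficient from that model.
3. Report the unadjusted slope, and how average initial ratings rank against average follow-up results by foot, as the total or foot-level association.
4. Limit the sentence on per-foot means and pair-wise differences to models that contain foot.

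The cost is one model term (six cells in place of one intercept, so five more parameters) and a few lines of text, with no change to data collection. The shared foot ranking no longer counts towards significance for the individual claim, but it stays visible under item 3. Power for the individual link itself is almost unchanged.

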2. The Four-Square Step Test (FSST): The FSST is a clinical outcome measure designed to assess dynamic balance. Participants are asked to step quickly in a 4-step pattern (i.e., forward, laterally, and backward) over canes (e.g., PVC piping) laid on the floor as per standard administration of the test. Participants complete the test twice while wearing their prescribed prosthetic foot, and the fastest of the two times required to complete the test is recorded. The FSST, including instructions, a practice trial, and the two timed trials, takes no more than 5 minutes to complete.
3. 4 Stage Balance Test (4SBT): The 4SBT is a performance-based test of static balance. There are up to four standing positions that get progressively more challenging to maintain for 10 seconds without moving their feet or needing support. The four positions are: feet side-by-side, placing instep of one shoe so it is touching the big toe of the other shoe; tandem stance of one shoe in front of the other with heel touching toe; and standing on one foot. Each position is described and demonstrated to the participant. Then, the participant may be guided and supported into assuming each correct position. When the participant is steady, they are timed to see how long they can maintain the position, but with close guarding ready to assist them if they should lose their balance and need to take a step. If the participant can hold a position for 10 seconds without moving their feet or needing support, they proceed to the next position. Participants are scored based on how many of the four stages they can safely complete.
4. Narrowing Beam Walking Test (NBWT): The NBWT is a performance-based test of balance for lower limb prosthesis users. It is comprised of four sets of low-to-the ground (i.e., approximately 4cm) beams that become increasingly narrow in width. Two practice trials and then three measured trials are performed with the distance walked on the beam averaged to produce a final score. The NBWT takes 3-5 minutes to complete. All trials will be done while the participant is wearing their prescribed prosthetic foot.
5. The L Test of Functional Mobility (L Test): The L test is a clinical measure designed to assess functional mobility. Participants will be asked to rise from a chair, walk 3 meters, turn at ninety degrees, walk 4 more meters and turn around, walk 4 meters, turn ninety degrees,

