and return to the chair, and to a seated position. Time to complete the task is recorded. The L test takes 1-2 minutes to complete. One practice trial and three timed trials will be performed and the average time will be used for analysis. All trials will be done while the participant is wearing their prescribed prosthetic foot.

Participants will be asked to walk on the treadmill (e.g., AC5000M medical treadmill, SciFit, Tulsa, OK) with their prescribed prosthesis and to choose three walking speeds: comfortable, slow, and fast. Participants will choose these speeds by increasing and/or decreasing the speed on the treadmill. This will allow participants to practice walking on the treadmill before trying the study prosthetic feet. They will be allowed to hold onto the safety bars at any time on the treadmill if needed in order to keep their balance. They will also be offered the option of using additional supports (e.g., gait belt, overhead safety harness) while walking on the treadmill throughout the study.

Participants will be assigned to the low mobility group (LM) or the high mobility group (HM). LM vs. HM grouping will determine which 3 prosthetic foot conditions each participant will wear during the testing protocol. This grouping will be informed by the results of the participant's 2MWT test, based on a cut-off distance of 113 meters as a guideline with clinical judgement. Although 113 meters translates to 371 feet, we use a cut-off of >375 feet for logistical purposes (i.e., distance between cones that participants will walk between is 75 feet). This is to ensure that participants will be using prosthetic feet that would likely be considered for their respective mobility levels in the clinical setting. For example, if a participant's 2MWT test score is marginal, the study research prosthetist will use other clinical indicators (e.g., balance, fatigue, quality of walking) to help inform the group assignment to ensure the participant can safely and comfortably complete the study activities for their respective group.

**Please note:** All prosthetic fittings for this study will be completed by a certified prosthetist, and they will be performed to meet normal clinical care standards. The treadmills described in the procedures below are equipped with safety rails and emergency stop features; participants will be given the option of using additional supports (e.g., gait belt, overhead safety harness) during the walking tests on this equipment.

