When ready, all participants will be asked to walk on the treadmill for up to a minute at each of their previously-selected walking speeds: slow, comfortable, and fast. Participants will be asked to repeat these walking tasks with the second and third randomized PFE mode or actual foot, when ready. Study staff will set the PFE to the subsequent modes or the prosthetist will fit the subsequent feet.

**Group ‘HM’** (high mobility): participants will then be asked to walk again for up to a minute at their selected comfortable walking speed, this time with the treadmill inclined up to 12% grade ( $\sim 7^\circ$ ) (similar to going up a moderate to steep hill). This inclination is the maximum amount of the treadmill, and is less steep than what has been commonly used for people with lower limb amputations in previous studies. We will stop the amount of inclination before 12% grade or adjust their walking speed, if needed. Next they will be asked to stand then walk, at a comfortable walking speed, on cross slopes on each side of up to 8.5% grade ( $\sim 5^\circ$ ) for up to a minute. This cross-slope inclination has been used in previous studies with this patient population. Finally, participants may be asked to walk at a comfortable walking speed on an uneven ground treadmill for up to one minute (Pro Slat Treadmill, Woodway, Waukesha, WI). For this treadmill, low-height rock holds resembling uneven ground have been fixed to the treadmill slats to present a challenging walking surface. This uneven treadmill surface is similar to conditions used previously to simulate walking in real-world uneven terrain conditions, including in people who have lower limb amputation. Participants will be offered a break prior to walking in each condition.

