**Group ‘LM’** (low mobility): participants will then be asked to walk again for up to a minute at their selected comfortable walking speed this time with the treadmill inclined up to 8.5% grade ( $\sim 5^\circ$ ) (based on the Americans with Disabilities Act (ADA) compliant ramp inclination angle). This inclination has been commonly used for people with lower mobility and lower limb amputations in previous studies, based on ADA regulations. We will stop the amount of inclination before 8.5% grade or adjust their walking speed, if needed. Next, they will stand then walk on the treadmill with cross slopes on each side of up to 5% grade ( $\sim 3^\circ$ ), and finally they will be offered the *option* of using the uneven ground treadmill for up to one minute.

When ready, participants will be asked to repeat these activities (e.g., inclined walking, cross slopes, uneven ground) with the second and third randomized PFE modes or actual feet. Between activities, participants will be given the opportunity to rest for as long as needed. During this time, they will be asked to complete a survey that includes questions about their preference, perceived stability, perceived foot stiffness, satisfaction and perceived mobility with the PFE modes or actual feet that they just walked with. These questions will occur following each activity as they complete it, or following all activities for items that refer to overall impressions about the foot that they just walked with.

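### The Aim 1 model has one within-participant error and no mobility-group term; if the low- and high-mobility groups are pooled and differ in spread, the .01 foot tests are too liberal in one group and too conservative in the other

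*Protocol*

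**What the plan says.** Section 2.6 (Statistical Analysis) gives the Aim 1 model as "prosthetic foot (the independent fixed effect) with random effects for study participant". It describes the error structure in one sentence: "These models account for non-independent data due to within-participant repeated measures by estimating separate between- and within-participant errors". It plans "pair-wise mean differences and 95% confidence intervals (CI) across the three feet". No term, stratum or variance for mobility group is mentioned.

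Section 2.5, Visit 1 makes the feet depend on the group: "LM vs. HM grouping will determine which 3 prosthetic foot conditions each participant will wear during the testing protocol". The same visit description gives five emulator foot modes in all, three per group with one shared. Groups are assigned mainly by a two-minute-walk cut-off of 113 m. At Visit 2 the groups also walk on different slopes: for HM, "this time with the treadmill inclined up to 12% grade"; for LM, "this time with the treadmill inclined up to 8.5% grade".

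The Power Analysis paragraph of Section 2.6 simulates 40 or 50 participants who all wear the same three feet, with one within-participant SD per outcome (2.7 ft for NBWT, 1.0 cm for MOS). It uses a type 1 error of .01.

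**The concern.** No participant wears feet from both sets apart from the shared one. In each group's set, the contrast between the two unshared feet is therefore informed by that group alone. In a pooled fit with one residual variance, its standard error is nevertheless built from the average of both groups' within-participant variances. The groups are defined by walking performance and tested on different slopes, so equal variances cannot be taken for granted.

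The two contrasts in each set that involve the shared foot have a further problem. Without a group term, the shared foot's mean is estimated from both groups, so part of any overall difference between LM and HM leaks into those contrasts.

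At stake are the .01 level and the interval coverage for the Aim 1 foot comparisons: false foot differences in the noisier group, and missed ones in the steadier group.

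**Working it through.** **1. What the plan's power figures assume.** Take an overall 2-df test of foot with means (0, 0, δ) and noncentrality n × (2/3) × δ²/σ², at level .01.
- NBWT, δ = 2, σ = 2.7: n = 40 gives 40 × 0.667 × 4/7.29 = 14.6; n = 50 gives 18.3.
- MOS, σ = 1.0: n = 40, δ = 1 gives 26.7; n = 50, δ = 0.7 gives 16.3.

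Power is 79.6%, 90.0%, 98.2% and 85.5% with the F form, and 82.6%, 91.7%, 98.8% and 87.5% with the chi-square form. The protocol states 81%, 91%, 98% and 87%. The stated figures therefore reproduce within two points for one sample, three feet and one common within-participant SD.

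**2. Size of a within-group contrast under a pooled error.** Inputs: 60 recruited less 20% leaves 48. An even 24 + 24 split is an assumption, as is r, the ratio of the noisier group's within-participant SD to the steadier group's. Set the steadier SD to 1.

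Pooled SD = √((n₁r² + n₂)/(n₁ + n₂)), with n₁ the noisier group. Size in the noisier group = 2P(Z > 2.576 × pooled SD/r). Size in the steadier group = 2P(Z > 2.576 × pooled SD). The steadier group's interval width is multiplied by the pooled SD.

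| r | pooled SD = steadier width factor | pooled SD/r | z, noisier | size, noisier | size, steadier |
|---|---|---|---|---|---|
| 1 | 1.00 | 1.000 | 2.576 | 1.0% | 1.0% |
| 1.25 | √1.281 = 1.13 | 0.906 | 2.333 | 2.0% | 0.4% |
| 1.5 | √1.625 = 1.27 | 0.850 | 2.189 | 2.9% | 0.1% |
| 2 | √2.5 = 1.58 | 0.791 | 2.036 | 4.2% | below 0.01% |

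A simulation of the five-foot model with pooled residual (20,000 runs, no true difference) gave 0.9%, 2.0%, 2.8% and 4.2% in the noisier group, in agreement.

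**3. Uneven split.** With 16 of 48 in the noisier group:
- r = 1.5: √((16 × 2.25 + 32)/48) = 1.190; divided by 1.5 this is 0.793; z = 2.044; size 4.1%.
- r = 2: √((16 × 4 + 32)/48) = 1.414; divided by 2 this is 0.707; z = 1.821; size 6.9%.

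If the noisier group is the larger (32 of 48), r = 1.5 gives √((32 × 2.25 + 16)/48) = 1.354; divided by 1.5 this is 0.903; z = 2.325; size 2.0%.

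**4. The shared foot.** Without a group term and with equal groups, the shared foot's mean is the average of the two groups' means. The unshared feet are shifted towards it by ρ = between variance/(between + within variance). With the NBWT SDs, ρ = 16.81/(16.81 + 7.29) = 0.698. A group difference D then biases each shared-foot contrast by (1 − ρ) × D/2 = 0.151 × D. For an assumed D of 4 ft this is 0.6 ft, even at equal within-participant SDs. Simulations that also estimated the variances gave 0.52 to 0.57 ft at SD ratios of 1.5 and 2.

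**5. Is a group main effect enough?** For the means, yes: five feet plus one group difference equals the six foot-by-group cells, and the simulated bias vanished. For the error, no: at r = 1.5 and nominal .05, size stayed near .10 in the noisier group and at .013 to .017 in the steadier one.

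**The case against.** The strongest reply is that Section 2.6 never says that LM and HM share a model. It speaks of three feet, which is what one group wears; a pooled model would have five. Read as one model per group, the plan already contains the remedy. This reading is open and stands as a limit on the point. It does not settle the matter, because the Power Analysis paragraph says that its models follow the methods section and simulates a single sample in which everyone wears the same three feet. If the analysis is by group, that simulation describes a different analysis: with 24 per group, the same F calculation gives NBWT power of about 48%. Either way the text needs a sentence.

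Second, the quoted sentence on errors explains how mixed models handle repeated measures; it does not assert equal variances across groups, and variance detail is often left to an SAP. That is fair. However, the protocol does state a model, and that model does not match the two-group, five-foot design.

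Third, nothing shows that the variances differ. This stands in full. The slopes do not enter ABC, NBWT or FSST, and gentler slopes for LM could equalise difficulty as easily as unbalance it.

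A reader might also infer that FSST, where "the fastest of the two times required to complete the test is recorded", should be analysed on the log scale because times spread more at higher levels. No figure in the protocol supports that; it is a modelling preference and no part of this point.

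**Conclusion.** The point holds conditionally. The stated model has a single within-participant error and no mobility group, while the feet are assigned by mobility group. Under pooling with unequal within-participant SDs, the noisier group's size at nominal .01 is about 2.0% to 4.2% for ratios of 1.25 to 2 at 24 + 24, and about 4.1% to 6.9% for ratios of 1.5 to 2 if that group is 16 of 48. At ratio 1 there is no distortion of the error. These figures rest on the assumed ratio, the assumed split and 48 completers.

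A reader might infer that the .01 level and the 95% intervals fail in both groups as planned. The documents do not support that: they give no SD by group, do not say which group is noisier, and do not say outright that the groups are pooled. Nor does every contrast draw on one group alone. In the pooled model without a group term, this is true only of the contrast between a group's two unshared feet; the shared-foot contrasts carry the mean bias shown above.

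**What to change.** State in Section 2.6 that Aim 1 foot contrasts are estimated within mobility group. Two forms would do: fit the model separately in LM and HM, or fit one model with foot-by-group means and group-specific between- and within-participant variances. Either form removes the shared-foot bias and gives each contrast its own group's error. A group main effect alone, with a common residual, is not sufficient.

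The text cost is one sentence. The statistical cost, if the SDs are in fact equal, is fewer error degrees of freedom:
- 24 per group: 2 × 23 = 46 instead of 2 × 46 = 92, so t(.995) is 2.687 against 2.630, and .01 intervals are about 2% wider.
- A group of 16: 2 × 15 = 30 degrees of freedom, t(.995) = 2.750, and intervals are about 4.6% wider.
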